## Methods/Design

### Intervention

Family-based behavioral social facilitation treatment (FBSFT) is founded on the principles of standard family-based behavioral treatment for obesity, which is the most well documented approach for childhood obesity [11].

FBSFT has an intensive treatment phase including weekly family meetings over 17 consecutive weeks with the same health care worker at the Obesity Outpatient Clinic (OOC), Haukeland University Hospital, Norway. All the health care workers on the multidisciplinary treatment team at the OOC are trained in FBSFT prior to treatment delivery. The multidisciplinary team consists of a pediatrician, nutritionist, physiotherapist, nurse and psychologist. Throughout the study period, the treatment team will have weekly meetings to discuss the patients in addition to monthly supervision sessions with the research team in St. Louis, MO, USA and Pittsburgh, PA, USA through video-conferences.

There are session-specific components and goals for each of the 17 sessions (see Table 1 for complete outline). The treatment targets healthy lifestyle changes in both the children and parents in the areas of diet, physical activity, sedentary activity, sleep and social function. The dietary and physical activity guidance used in the study is based on the Traffic Light Diet [40] in which foods and activities are organized into green, yellow and red groups. Green meaning “go,” yellow meaning “sometimes” and red meaning “limit.” The treatment focuses on implementing the behavior change across all the different settings in the family members’ daily lives (i.e., within the home/family environment, peer network environment, community environment).

**Table 1 Tab1:** Session topics in family-based behavioral facilitation treatment (FBSFT)

Phase	Session	FBSFT Topic
1. Individual and Home Contex	1-2	Introduction to the treatment; plan for the Traffic Light Diet; personalized treatment plan
	3	Healthy and regular eating, communicating with the family about lifestyle changes
	4	Sedentary activity; sleep routines
	5	Physical activity; lifestyle activity
	6	Creating a healthy family and home environment; problem solving skills
	7	Healthy self-instructions; emotions/stress and eating behavior
2. Peer Contex	8	Peers as a support for healthy behaviors (arranging healthy activities with others); assessment of social network
	9	High risk situations (parties, holidays and vacations); prompts for eating and physical activity

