	10	A healthy peer environment; communicating with peers about new and healthy habits
	11	Taking on Teasing
3. Community Contex	12	Physical activity and the assessment of RED food in the environment/neighborhood
	13	To be active in your neighborhood; join groups or teams; to elicit support for healthy habits in your neighborhood/environment
	14	To fight weight stigmatization; influences from the media; to build a positive self-image and body image
	15	High risk situations (restaurants and fast food); to focus on healthy habits at school and work
4. Cross-contextual	16	To plan for healthy habits; relapse prevention and consolidating skills across different contexts
	17	Reviewing goals and skills; ending well; planning ahead

Through the treatment sessions, the families are taught a set of behavioral and cognitive techniques for promoting healthy behavior change and dealing with mechanisms that maintain unhealthy lifestyle behaviors:Self-monitoring. Both the parents and children monitor their eating, weight and activity on a week-to-week basic going through the intensive treatment phaseGoal setting, planning and reward systemsStimulus controlEmotion regulation strategiesReframing negative automatic thoughtsCommunication and interpersonal skillsParenting strategiesHealthy modeling from the parentsHealthy methods of self-evaluation and self-assertion

After the intensive treatment phase, the families receive monthly follow-up treatment for 18 months through collaboration between specialty and primary care: monthly follow-up sessions with their school nurse (primary care) and follow-up sessions every third month at the OOC. The focus for these sessions is maintenance of healthy habits.

For families assigned to standard treatment (treatment as usual, TAU), the treatment consists of a post-assessment meeting between a health care worker at the OOC and the family, agreeing on behavioral goals for changing lifestyle, a plan for the implementation of new behaviors and goals for weight loss. Each family also participates in monthly counselling session with their local health care nurse to work on implementing these goals, including measuring their weight change, and also meets every third month for sessions at the OOC for assessments, evaluation of progress and revision of goals. TAU is delivered over the course of 12 months.

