### Study objectives and hypotheses

The objectives and hypotheses of the current study are:To evaluate the effect of FBSFT compared to TAU for severe childhood and adolescent obesity in a common health care setting. The primary outcome is weight status, assessed as BMI, BMI standard deviation scores (SDSs) and percentages above the IOTF cut-off for overweight (%IOTF-25) [41]. Secondary outcomes are other weight-related anthropometric measurements (waist circumference (WC) and Waist-to-height ratio (WHtR) and corresponding SDSs), body composition (BIA, DXA), blood test, blood pressure, eating habits, sleep, physical activity as well as psychological well-being and parenting style.○ We hypothesized that FBSFT will be superior to TAU in improving these parameters both during the intensive treatment period and during the follow-up period.
To identify predictors of treatment success and treatment drop out with a focus on family variables, socioeconomic status, social network and mental health.○ We expect children from families in which both parents participate in treatment to demonstrate better weight loss outcome and have lower dropout rate.○ We expect children of parents living together to demonstrate better treatment effects and have lower dropout rate.○ We expect that parental (self-reported) weight status will influence treatment effects and dropout rate; higher BMI category will predict poorer treatment effects and higher dropout rate.○ We expect that lower socio-economic status and limited social network will predict poorer treatment effects and higher dropout rate.○ We expect poorer treatment effect and higher dropout rate among participants with psychological comorbidities.
To evaluate experienced barriers to treatment, and how these factors influence children’s and parents treatment response. Barriers to treatment are classified into four groups: competing activities/life stressors, relevance of treatment, treatment issues (logistics) and critical events.○ We expect lower degree of competing activities/life stressors to predict better treatment response and lower dropout rate.○ We expect higher degree of experienced treatment relevance to predict better treatment response and lower dropout rate.○ We expect lower degree of treatment issues and lower number of critical events to predict better treatment response and lower dropout rate.

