## Planned data analysis

A two-way MANOVA with one repeated-measure factor (Time: pre-intervention/post-intervention), and one between-group factor (Treatment Group: FBSFT vs. TAU) will be conducted to assess the impact of treatment on primary and secondary outcomes.

A one way within-subjects MANOVA will be used to analyze the effect of time (pre-treatment, post-treatment, 12-, 18-, 24 months post treatment) on primary and secondary outcomes.

In order to identify factors associated with treatment success and treatment drop out, multiple regression analyses will be conducted. The dependent variables are %IOTF-25 and drop-out status (yes/no). The predictors are: both parents participating in treatment, parental marital status, self-reported parental weight, socio-economic status and social network, psychological comorbidities.

In order to identify barriers to treatment and how these barriers influence children’s and parents’ treatment response, multiple regression analyses will be conducted. The dependent variable is %IOTF-25. The predictors are: competing activities/life stressors, relevance of treatment, treatment issues (logistics) and critical events.

Intention-to-treat analyses will be conducted and effect sizes calculated for treatment effects.

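### The barrier regression leaves out treatment arm, so if the two arms are pooled its associations with %IOTF-25 are open to confounding by arm

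*Protocol article*

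**What the plan says.** All references are to the protocol article.

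- **Barrier model (Planned data analysis).** "The dependent variable is %IOTF-25", and "The predictors are: competing activities/life stressors, relevance of treatment, treatment issues (logistics) and critical events".
- **Predictor model (same section).** The outcomes are %IOTF-25 and dropout. "The predictors are: both parents participating in treatment, parental marital status, self-reported parental weight, socio-economic status and social network, psychological comorbidities".
- **Arm.** Neither list contains it. The same section does name treatment group as a factor in the MANOVA of treatment effect. Neither regression says which families or which treatment period it covers.
- **Session load (Intervention).** FBSFT has "weekly family meetings over 17 consecutive weeks" at the hospital clinic. A TAU family sees the local nurse monthly and "also meets every third month for sessions at the OOC for assessments, evaluation of progress and revision of goals".
- **Hypotheses (Study objectives and hypotheses).** FBSFT is expected to be superior on weight status, which includes %IOTF-25. Barriers are described as experienced, and include logistics and the perceived relevance of treatment.
- **Design (Trial design, Sample size, Randomization).** 60 families per arm are randomised to FBSFT at once or after one year of TAU. The regression is sized at 55 persons, testing one predictor in a model with five.

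**The concern.** A barrier score collected during or after treatment is not protected by randomisation. A family asked to attend weekly at a hospital may report more logistic trouble than one seen mainly by a local nurse, and may rate the relevance of treatment differently. If FBSFT also lowers %IOTF-25, as hypothesised, arm influences both predictor and outcome, and the listed model does not hold it constant.

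The distortion can go either way. If FBSFT families report more logistic barriers and also lose more weight, barriers will tend to go with better response. That works against the expectation that "We expect lower degree of treatment issues and lower number of critical events to predict better treatment response and lower dropout rate". If FBSFT families rate treatment as more relevant, the same mechanism gives unearned support to the relevance hypothesis. Barriers are one of the numbered study objectives, so a reader would take these coefficients as findings about families when they may partly reflect which treatment the family received.

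**Working it through.** **1. The plan's own figure.** Regression sample size, by the noncentral F with alpha 0.05 and power 0.80 (stated for the group-by-time calculation and assumed to carry over): df1 = 1, df2 = N − p − 1, noncentrality f² × N. With f² = 0.15, p = 5 and N = 55, df2 = 49, noncentrality = 8.25 and power = 0.8039. The stated 55 reproduces, provided the 0.15 printed as f is read as f².

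**2. Is there room for arm?** With arm added, p = 6 and df2 = 48. Power at N = 55 is 0.8036, so the required N stays 55.

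**3. Session load to month 6.** FBSFT: 17 planned clinic sessions. TAU: 6/3 = 2 clinic sessions and 6 nurse sessions, 8 in all.

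**4. Size of the bias.** The document gives no arm difference in barrier scores and no expected standardised effect on %IOTF-25, so both are assumptions. Let d be the arm difference in the barrier score and e the arm difference in the outcome, in within-arm SDs, with equal arms and no true barrier effect. Then:

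- covariance of barrier and outcome = d × e / 4
- variance of barrier = 1 + d²/4
- spurious slope = (d × e / 4) / (1 + d²/4)

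The slope is negative if FBSFT raises the barrier score and lowers %IOTF-25. False-positive rates come from simulation (60 per arm, 20,000 runs per row, one barrier in the model):

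| d | e | Spurious slope (absolute) | Arm omitted | Arm included |
|---|---|---|---|---|
| 0 | 0.5 | 0 | 5.1% | 5.1% |
| 0 | 0.8 | 0 | 5.3% | 5.0% |
| 0.3 | 0.5 | 0.0375/1.0225 = 0.037 | 6.9% | 5.3% |
| 0.5 | 0.5 | 0.0625/1.0625 = 0.059 | 9.6% | 4.8% |
| 0.5 | 0.8 | 0.1000/1.0625 = 0.094 | 16.2% | 4.8% |
| 0.8 | 0.5 | 0.1000/1.1600 = 0.086 | 16.3% | 4.8% |
| 0.8 | 0.8 | 0.1600/1.1600 = 0.138 | 33.1% | 5.0% |

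The slope is zero when either d or e is zero.

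**5. Against an effect of the planned size.** On this scale f² = 0.15 is a slope of √0.15 = 0.39. A spurious slope of −0.04 to −0.14 would reduce it to about 0.35 to 0.25.

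**6. Which predictors are exposed.** The rows with d = 0 stand for anything balanced by randomisation. Marital status, parental weight, socio-economic status, social network and psychological comorbidity fall there if taken at baseline. Whether both parents take part may not: if it is recorded as actual participation, it arises after allocation and can depend on arm.

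**The case against.** The strongest reply is that pooling is inferred. The section does not name the families or the period. Every family eventually receives FBSFT, and 55 persons would fit within one arm of 60, so an FBSFT-only analysis is compatible with the text. The contrast in session load would then fall away. This stands as far as it goes: the confounding is conditional on pooling. But the text does not establish the restriction either, and arm B would still enter FBSFT after a year of TAU.

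A second reply is that a condensed article names only the predictors of interest and leaves adjustment covariates to a fuller document. That is possible. Against it, each model is introduced by an explicit list, the neighbouring MANOVA names treatment group, and the five predictors in the sample-size statement match the five comma-separated items in the predictor list, with no place for arm.

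Third, the sizes are assumed. This stands. At the mild end (0.3 and 0.5 SD) the inflation is small, 6.9% against 5.3%. The Background itself says that more than modest weight loss is hard to achieve in adolescents with severe obesity. The direction is also assumed: missed FBSFT sessions can be rescheduled, combined or held by phone, which eases logistics. And the simulation has one barrier, where the plan enters four together.

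A reader might go further and infer that the dropout analysis is confounded by arm as well. The document does not support that in general. The barrier regression does not model dropout, and the predictors of dropout, taken at baseline, are balanced in expectation; only participation by both parents is a possible exception.

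**Conclusion.** The point holds in a limited form. If the barrier regression is run as listed on all randomised families, its coefficients are open to confounding by arm, because barriers arise after randomisation and the protocol expects arm to change the outcome. Participation by both parents can be affected in the same way. For the other predictors, taken at baseline, leaving out arm costs precision but does not confound.

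Under the assumed arm differences, the false-positive rate for a barrier with no effect is about 7% to 33%, against about 5% with arm in the model. If either arm difference is zero there is no bias.

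It would be tempting to say that the omission reverses the barrier findings. The figures do not show this: over the assumed range the spurious slope weakens an effect of the planned size without changing its sign. The randomised comparison of FBSFT with TAU includes treatment group and is unaffected.

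**What to change.** State which families and which treatment period enter each regression. Then take one of two routes:

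- **Arms pooled.** Include randomised arm as a covariate in the barrier regression and in the predictor regressions, with arm-by-barrier terms reported as exploratory.
- **FBSFT exposure only.** Restrict the regressions to arm A from the start and arm B from month 12, say so, and still adjust for arm because arm B has had a year of TAU.

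The cost is one degree of freedom per model for the arm term and a sentence or two of text. Arm is already known for every family, and the required sample size for the regression stays 55.

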Dropout is a substantial concern in treatment of both adult and pediatric obesity [11, 29, 30], but only a limited number of studies have examined the predictors for dropout [29, 31, 32]. Studies show mixed results regarding barriers to treatment participation. Some studies have found higher number of barriers in families who end the treatment program prematurely [32, 33], while another found few differences in degree of barriers among treatment completers compared to non-completers [31]. Post-treatment reported barriers in prior studies include high degree of family stressors, parent-adolescent conflict, lack of time and interest, interference with school schedules, disappointment with amount of weight-loss, and treatment taking place too far from home [31, 32, 34]. Further research on predictors for dropout and barriers to treatment participation, both among non-completers and completers, has important implications for clinical practice [30].

Another subject of clinical importance is to identify pre-treatment factors related to poorer treatment response. Together with knowledge about predictors for dropout and barriers to treatment participation, these factors can identify at risk groups and tailor childhood obesity treatment to increase treatment response. Several pre-treatment factors have been associated with weight loss outcomes in previous research on childhood obesity treatment [30, 31, 35–38], including child age, gender, child initial weight status [36, 38], child mental health problems [36, 37], and parents’ degree of motivation [30, 31, 35, 36]. However, there seems to be a lack of studies investigating the influence of family variables and broader social network support as predictors of treatment response.

The aim of this paper is to describe and explain the design and evaluation of the Family-based behavioral treatment of childhood obesity (FABO)−study targeting children and adolescents with obesity and their families. The description of the study protocol follows the checklist of the CONSORT statement for randomized trials [39] (Additional files 1 and 2).

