### Inclusion criteria

The sample will consist of 120 children and adolescents (aged 6–18 years) referred to the OOC by their general practitioner. Criteria for admission to the clinic is an International Obesity Task Force (IOTF) BMI ≥ 35, or ≥ 30 [41] with obesity related co-morbidity. The child/adolescent participates in the treatment together with her/his family, such that both the child and a least one of the parents agree to actively participate in the treatment.

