### Sample size

One hundred twenty families will be recruited, with 60 families in each treatment arm. Power estimates were calculated using G*Power, version 3.1.3. [42, 43] With two treatment groups (TAU, FBSFT), 3 measurement points (pre-treatment, 6 months post-treatment and 12 month post-treatment) and a correlation of 0.5 between the measurement points, alpha .05, power .80, a small (*f* = 0.10), moderate (*f* = 0, 25) and high (*f* = 0.40) effect size would demand respectively sample sizes of 164, 28 and 12 participants to detect a significant group X time interaction on the primary outcome. For regression analysis of predictors of treatment outcome, a small to moderate effect size is expected (*f* = 0.15), and when testing the increase in R^2^ by adding 1 predictor to an analysis including 5 predictors in total, a sample size of 55 persons will be needed.

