### Psychological measures

The following five questionnaires will be used in the study:

*The Child Behavior Checklist (CBCL)* [49], a 138-item scale assessing behavioral and emotional symptoms in children that has both a child/youth and parent form. Several studies have provided evidence of the instruments psychometric properties and stability [49–51].

*Children’s Depression Inventory (CDI)* [52], a 27-item self-report measure assessing the cognitive, affective and behavioral symptoms of depression in children (7–17 years). The psychometric properties of the scale have generally been found to be acceptable [53, 54].

*Self-Perception Profile for Children (SPPC)* [55], a self-report measure of self-perception or self-esteem in children aged 8 to 14 years widely used for research purposes. The questionnaire includes 36 statements and the children are asked to evaluate to which degree the statement fits their thoughts about themselves. The internal reliability has been demonstrated to be high [56].

*The Dutch Eating Behavior Questionnaire Child version (DEBQ)* [57], a measure of disordered eating behaviors in children and youth. DEBQ consists of three sub-scales: emotional eating, external eating, and restrained eating. The questionnaire is increasingly used for research on youth with overweight and psychometric properties have in general been found acceptable [58, 59].

*The Youth Eating Disorder Examination-Questionnaire (YEDE-Q)* [60], a self-reported measure of eating patterns and eating disorder psychopathology. The YEDE-Q is a self-report version of the Child Eating Disorder Examination (ChEDE) and was designed to include measurements of binge eating in youth [61]. The YEDE-Q has been validated using the ChEDE as an assessment of eating-related pathology in overweight youth [61].

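### The planned MANOVAs use complete cases by default, so they do not by themselves deliver the promised intention-to-treat analysis

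*Protocol article*

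**What the plan says.** The Planned data analysis section fixes the method for the group comparison: "A two-way MANOVA with one repeated-measure factor (Time: pre-intervention/post-intervention), and one between-group factor (Treatment Group: FBSFT vs. TAU) will be conducted". It applies this to the primary and secondary outcomes. A second, one-way within-subjects MANOVA covers the effect of time over five measurement points, from pre-treatment to 24 months. The section closes with "Intention-to-treat analyses will be conducted and effect sizes calculated for treatment effects". It names no method for missing data, and does not say whether the outcomes enter one model, several models by domain, or one model each.

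Missing data are expected. The Background says "Dropout is a substantial concern in treatment of both adult and pediatric obesity". Drop-out status is a dependent variable in the planned regressions. The section on adherence strategies sets up monthly checks and reminders for missing assessments. The Sample size section plans 120 families and mentions no allowance for dropout.

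On age, the Inclusion criteria state "The sample will consist of 120 children and adolescents (aged 6–18 years", while Psychological measures describes the SPPC as "a self-report measure of self-perception or self-esteem in children aged 8 to 14 years" and the CDI as covering ages 7 to 17.

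**The concern.** A repeated-measures MANOVA works on one row per child holding every dependent variable at every time level. A child with one empty cell is removed unless something is done first. Run as named, both analyses are restricted to children with complete data, whereas an intention-to-treat analysis should account for all randomised children in their allocated arms.

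This matters for two reasons. First, complete-case estimates are open to bias when the children who leave differ from those who stay. The arms differ in contact burden: 17 weekly clinic sessions in FBSFT, against monthly local counselling and three-monthly clinic visits in TAU. Unequal dropout is therefore plausible. Second, information is thrown away. A child measured at baseline, 6 and 12 months but not at 18 months contributes nothing to the five-visit model. A child with a valid BMI but one missing questionnaire contributes nothing to a joint model containing both.

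**Working it through.** **Inputs from the article.** Sample size: "One hundred twenty families will be recruited, with 60 families in each treatment arm"; "3 measurement points (pre-treatment, 6 months post-treatment and 12 month post-treatment"; "a correlation of 0.5 between the measurement points, alpha .05, power .80"; stated totals of 164, 28 and 12 for f = 0.10, 0.25 and 0.40. Trial ages 6–18, SPPC 8–14, CDI 7–17. Five visits, four of them after baseline. **Assumptions.** The article gives no dropout rate and no age distribution, so both are varied below.

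**1. The plan's own figures.** Group-by-time interaction, noncentral F, with λ = f²·N·m/(1−ρ), df1 = (k−1)(m−1), df2 = (N−k)(m−1), k = 2, m = 3, ρ = 0.5:
- f = 0.10, N = 164: λ = 0.01 × 164 × 3/0.5 = 9.84, power 0.805.
- f = 0.25, N = 28: λ = 0.0625 × 28 × 6 = 10.5, power 0.812.
- f = 0.40, N = 12: λ = 0.16 × 12 × 6 = 11.52, power 0.810.

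The stated 164, 28 and 12 are reproduced.

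**2. Primary weight outcomes, pre/post.** BMI, BMI SDS and %IOTF-25 carry no questionnaire age limit, so complete cases = 120 × (1 − dropout): 108, 96, 84 and 72 at 10%, 20%, 30% and 40%. The planned pre/post test has m = 2. For a single outcome, λ = f² × N × 2/0.5 = 4f²N:
- N = 120: power 58% at f = 0.10 (λ = 4.80), above 99% at f = 0.25; detectable f at 80% power 0.129.
- N = 96: power 49% at f = 0.10 (λ = 3.84), above 99% at f = 0.25; detectable f 0.144.

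**3. Five-visit MANOVA.** With independent loss p at each of four post-baseline visits, the complete share is (1 − p)⁴:
- p = 10%: 0.9⁴ = 0.656, about 79 of 120.
- p = 20%: 0.8⁴ = 0.410, about 49 of 120.

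If the same children miss every later visit, the complete share is simply 1 − p (90% or 80%), so independence gives the lower figures of the two.

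**4. Age-limited scales, only if they enter a joint model and are not scored out of range.** For SPPC pre/post, a child must be at least 8 at baseline and still in range 6 months later.
- Uniform ages, whole-year reading (6.0 to 19.0; SPPC 8.0 to 15.0): baseline 7/13 = 54% (65 children); pre/post (14.5 − 8)/13 = 50% (60); through 24 months (13 − 8)/13 = 38% (46).
- Uniform ages, strict reading (6.0 to 18.0; SPPC 8.0 to 14.0): baseline 6/12 = 50% (60); pre/post 5.5/12 = 46% (55); through 24 months 4/12 = 33% (40).
- Truncated normal ages, mean 10–14, SD 2–4: 55% to 90% in range pre/post.

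The pre/post loss thus runs from 10% to 54%. Adding 20% dropout to the uniform cases leaves 60 × 0.8 = 48 or 55 × 0.8 = 44. For CDI with uniform ages, 11/13 = 85% or 10/12 = 83% are in range at baseline, a loss of 15% to 17%.

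**The case against.** The strongest reply is that the article never says incomplete children will be dropped. MANOVA can be run on imputed data, and a missing-data method is commonly left to the full protocol or the SAP, neither of which is shown. That is right as far as it goes: a reader might infer that the two sentences contradict each other, and they do not. What remains is that the model is fixed here, and it is one that discards partial data. A later plan would have to add imputation or replace the model to honour the intention-to-treat sentence.

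A reader might also infer that about half the sample disappears. That needs three things together: SPPC in one joint model, no SPPC score outside ages 8–14, and ages spread evenly over 6–18. The article states none of them. It gives the instrument's age range, not a rule on who completes it. SPPC and CDI are secondary outcomes, and weight status analysed separately loses no child to age.

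A third tempting reading is that completers' estimates would favour FBSFT. No dropout by arm is given. Sessions can be rescheduled, combined or held by phone, and arm B is promised FBSFT after a year, which may affect retention in TAU. The direction of any bias is conjecture.

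Finally, the five-visit MANOVA is a within-subject analysis of time. Its losses bear on the description of long-term course, not directly on the randomised comparison.

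**Conclusion.** The point holds in a limited form. The named MANOVAs are complete-case analyses by default and do not by themselves provide the promised intention-to-treat analysis, in a trial that calls dropout a substantial concern and models it as an outcome.

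For the primary comparison the cost is moderate: 96 of 120 children at an assumed 20% dropout, with power at f = 0.10 falling from 58% to 49% and hardly changing at f = 0.25. There is also an unquantified risk of bias, of unknown direction. The five-visit analysis is the most exposed, at about 41% to 66% complete under independent loss of 20% to 10% per visit. The age-related loss (10% to 54% for SPPC pre/post, 15% to 17% for CDI at baseline) is conditional on a joint model and on no scoring out of range, and should not be quoted as a property of the plan.

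**What to change.** Replace both MANOVAs with a likelihood-based linear mixed model for each outcome: group, visit and group-by-visit, baseline included, unstructured covariance, using all available visits of every randomised child in the allocated arm. Read the FBSFT-versus-TAU contrast from the visits before arm B moves to FBSFT; later visits describe the course over time. Add a sensitivity analysis in which dropouts are not missing at random, for example reverting toward baseline. Analyse SPPC and CDI separately, in children within the stated age range, and report the reduced N. If the sponsor prefers to keep MANOVA, multiple imputation would also reconcile it with the intention-to-treat sentence, but the method would have to be stated.

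The cost is a change of wording and a few hours of programming in standard software, with no new data. Two limits remain. The mixed model still assumes data are missing at random, hence the sensitivity analysis. And a child seen only at baseline adds little to the treatment contrast under any model; most of the gain comes from children with some later visits or some outcomes missing. The change should be fixed before allocation is unblinded for analysis.
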